## **2.5. Early Withdrawal of Subjects: N/A**

## **2.6. Vulnerable Populations: N/A**

## **2.7. Populations vulnerable to undue influence or coercion: N/A**

# **3. STUDY DESIGN:**

## **3.1. Design:**

**AIM 1: Determine the effectiveness of the Resilience Project AR2 on opioid overdose outcomes for EMS patients who refuse hospital transport after overdose.**

a. **Rationale and theoretical framework:** Commonly, in Philadelphia and elsewhere, people who refuse transport to an ED after their overdose are at particular risk for repeat overdose and death as they typically do not receive, at the time of the event, referral to treatment, counseling, or take-home naloxone that could be obtained through “warm handoff” programs at the hospital. This gap in prevention and treatment may contribute to significant levels of morbidity and mortality. The AR2 targets this unique and high-risk group of opioid users at the time and place of their overdose. Our evaluation of the AR2 will be guided by the Quality Framework for Emergency Treatment of Opioid Use Disorder as outlined by Samuels and colleagues. In this framework, emergency care harm reduction interventions and treatment can be implemented and evaluated through a Donabedian structure-process-outcome perspective to assess a prehospital emergency approach to opioid use. In Figure 7 we adapt this framework to the AR2 in which high quality prehospital care has the structural capacity to provide take-home naloxone and referral to evidence based treatment programs with immediate availability, harm reduction and treatment referral processes are delivered with high fidelity, and people who overdose are linked to care and subsequently are less likely to experience non-fatal and fatal overdose outcomes.

- b. **Study design:** This quasi-experimental evaluation of the effectiveness of the AR2 will compare rates and time to treatment linkage, non-fatal overdoses within 60 days, and deaths within 24 months for people in the Kensington neighborhood who overdose, refuse EMS transport, and receive AR2 services with those who refuse EMS transport but for whom the AR2 is not dispatched.
- c. **Intervention:** The AR2 is a neighborhood-based intervention launched by three City of Philadelphia public agencies (PDPH, PFD, MDO), supported by the City of Philadelphia and a multi-year SAMHSA implementation grant (RFA SP-17-005), which does not provide capacity for rigorous scientific evaluation. Please note the Penn team is not directly involved in implementing or running the AR2. The AR2 brings a specialized response unit, staffed by a paramedic lieutenant, a social worker, a case manager and a certified recovery specialist, to the scene for 9-1-1 calls that indicate overdose in the Kensington neighborhood. Each AR2 dispatch includes a paramedic and various combinations of other support staff. The AR2 accompanies – but do not replace – conventional ambulances dispatched for these calls. The ARU is dispatched between 10 AM and 6 PM, 7 days/week for all presumed overdose EMS calls in Kensington. While many overdoses occur during the day, many also occur at night. Daytime staffing of the ARU was initiated for logistical and budgetary purposes with the plan to extend hours if deemed effective. If the ARU arrives to the patient before the ambulance, the ARU team initiates medical treatment, including administration of naloxone.
- The ARU delivers six core services on scene to patients who refuse transport to the hospital: 1) dispensing of take-home naloxone, 2) referral to a treatment facility that has immediate availability and can provide MAT, 3) transportation to the facility, 4) family engagement, 5) acquisition of patient telephone information for follow-up, and 6) connect over the phone with the patient in follow-up. If the ARU vehicle arrives after the ambulance, ARU staff provide backup support focused on harm reduction and linkage to care as needed. ARU interventions can occur whether or not naloxone has been administered. These services are, in other settings, limited to hospital-based and fixed community-based sites and are largely outside of the scope of traditional EMS care. While EMS has the capacity to provide take-home doses of naloxone (depending on availability), anecdotally uptake has been low in Philadelphia. Moreover, traditional EMS does not have the capacity to refer patients to treatment programs, provide transportation directly to treatment programs, or follow up with people who have experienced overdose. These patients, many of who are revived by naloxone, are at particularly high risk of repeat overdose and death and do not typically have access to harm reduction or OUD treatment in locations where they live and/or use drugs. Based on total EMS encounters for overdose in Philadelphia -- including those that receive naloxone and those that don't -- and our knowledge of EMS transport refusal rates in Kensington (approximately 25%-30%), we estimate between 300 and 500 ARU engagements per year, or 600-1000 engagements over our two-year study period.

- d. **Comparator Group:** We will use EMS encounters for drug overdose that do not include AR2 arrival on-scene as a comparator group. There are multiple reasons for an EMS-only patient encounter for overdose, e.g., the 1) call is for an overdose outside of the geographic AR2 dispatch zone; 2) EMS dispatch occurs during an time in which the AR2 is not active (6PM-10AM); the 3) AR2 is not dispatched because an overdose is not presumed based on the dispatcher assessment; the 4) AR2 is unavailable because it is on-scene at another call; or 5) the ambulance and/or patient leaves before the AR2 arrives on-scene. The reasons for a patient to receive EMS-alone are largely determined by timing and location of the overdose as opposed to endogenous patient or provider-level characteristics. We will construct multiple comparison encounters based on these five reasons. Specific decisions will depend on the frequency we observe in our data collection. Ideally, encounters that are non-AR2 because of a competing simultaneous call represent an ideal comparator since they match the AR2 call in terms of time, date, and location. These simultaneous encounters will represent the primary comparators. As a secondary comparator group, we will also construct comparison encounters near a temporal or spatial AR2/non-AR2 boundary. Such discontinuities are also useful for identifying causal effects through a difference or difference-in-difference analysis.

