2  
3 **PRINCIPAL INVESTIGATORS:** [name] MS, [name] MS

4 **PROTOCOL TITLE:** Studying the PhilAdelphia Resilience Project as a Response to Overdose  
5 (SPARROw)

6  
7 **1. INTRODUCTION AND PURPOSE:**

8  
9 **1.1. Objectives:** The objective of this proposal is to evaluate the effectiveness and  
10 implementation of two City of Philadelphia Resilience Project programs to reduce  
11 opioid overdose: (1) the Alternative Response 2 (AR2) that accompanies ambulances  
12 responding to overdoses and aims to deliver harm reduction and care linkage to people  
13 who refuse hospital transport, and (2) blight remediation of abandoned buildings and  
14 land. This application leverages a natural experiment within the Resilience Project  
15 implementation to evaluate its impact on overdose outcomes.

16  
17 We propose to address the following Specific Aims:

18  
19 **SA1: Determine the effectiveness of the Resilience Project AR2 on opioid overdose**  
20 **outcomes for EMS patients who refuse hospital transport after overdose.** Using a  
21 quasi-experimental design, we will compare the proximal overdose outcomes (rates and  
22 timing of treatment linkage) and distal overdose outcomes (non-fatal overdoses within  
23 60 days and overdose deaths within 24 months) for patients who receive AR2  
24 engagement compared to those who, due to timing or location restrictions, receive  
25 traditional EMS care alone.

26  
27 **SA2: Evaluate the impact of Resilience Project blight remediation activities on**  
28 **fatal and non-fatal opioid overdose.** Blight remediation activities vary across time and  
29 space in Kensington. We will use a difference-in-difference design to compare fatal and  
30 non-fatal overdoses in the 60 days before and after any given remediation effort  
31 compared to the same time period in two nearby locations that did not get remediated  
32 but had comparable pre-blight remediation overdose rates. We will select one control  
33 location from within Kensington and one just outside the Resilience Project geographic  
34 boundary.

35  
36 **SA3: Evaluate implementation of the Resilience Project by a) characterizing the**  
37 **fidelity of the AR2 intervention in Kensington, b) measuring factors that moderate**  
38 **AR2 fidelity, including blight, c) assessing barriers and facilitators to AR2**  
39 **implementation, and d) determining the costs for AR2 and blight remediation**  

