## **2.2. Key Inclusion Criteria:**

**Inclusion criteria for the intervention group include all AR2 encounters where:**

- The encounter is for a presumed overdose
- Patients are at least 18 years of age
- Located within the Kensington area (AR2 dispatch zone)
- From May 1, 2019 to April 30, 2021 (24 months)

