Staffing combination (inner setting) is self-recorded by the AR2 providers. Due to varying AR2 staffing from shift to shift, we anticipate variability in dosage and fidelity by different crews, which will be unconfounded with encounter features, conditional on time and place. Our primary approach will be regression models, logistic regression for 0/1 outcomes and a proportional hazards model for time-to-event outcomes, in which our measures of dosage and fidelity are covariates. The power calculations for these analyses are identical to the Aim 1 power analysis for comparisons across time discontinuities. Rather than comparing across time periods, we will be comparing across high/low dose and high/low fidelity. Certain patients may be more receptive to AR2 services causing the AR2 to provide a greater dosage and maintain higher fidelity to the AR2 model. While we have no direct measure of “receptivity,” we will use a collection of patient features potentially correlated with receptivity including patient substance abuse profile, number of prior overdoses, age, race, and sex. We will use propensity score weighting to reweight high dosage patients so their features collectively resemble the features of low dose patients. Outcome models using these weights will estimate the treatment effect of receiving a low dose, answering what would happen to low dose patients if instead they were give a high dose of AR2 services. Similarly, we can reweight patients receiving high fidelity AR2 response to resemble low fidelity AR2 response, so that the outcome model estimates the effect of receiving low fidelity for those patients who actually received low fidelity AR2. Although dosage and fidelity are not 0/1 measures, we will consider dichotomizing them if high/low dosage and high/low fidelity have clear boundaries in practice.

- d. **Evaluating barriers and facilitators to AR2 implementation:** In order to supplement the approach to implementation analysis described above, we aim to add a qualitative approach to understanding and describing provider and process level individual perspectives that may influence implementation. This additional approach acknowledges that, while guided by theoretical implementation frameworks, a purely quantitative approach could miss important contextual aspects of implementation that

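### Aim 1 defines the AR2 arm by services received in one place and by all AR2 encounters in another; if the first is applied, only one arm is filtered and a false benefit could result

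*Protocol*

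**What the plan says.** The protocol describes the Aim 1 arms in several places.

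- **Section 1.1, SA1:** outcomes are compared "for patients who receive AR2" engagement against those who, because of timing or location, have traditional EMS care only.
- **Section 3.1, Aim 1, b (Study design):** the AR2 arm is "people in the Kensington neighborhood who overdose, refuse EMS transport, and receive AR2 services", compared "with those who refuse EMS transport but for whom the AR2 is not dispatched".
- **Section 2.2 (Key Inclusion Criteria):** "Inclusion criteria for the intervention group include all AR2 encounters where" four conditions hold: presumed overdose, age, place and date. Services received and transport refusal are not among them. Section 2.3 does not list declining services as an exclusion.
- **Section 3.1, Aim 1, d (Comparator Group):** "We will use EMS encounters for drug overdose that do not include AR2 arrival on-scene as a comparator group". One listed reason for being EMS-only is that "the ambulance and/or patient leaves before the AR2 arrives on-scene". The primary comparators are simultaneous calls.
- **Section 5.5, Aim 1 Analysis, b (Paired encounter analysis):** pairs are built starting from each AR2 encounter, with no condition on services.
- **Section 3.1, Aim 3, c:** "Certain patients may be more receptive to AR2 services causing the AR2 to provide a greater dosage". The same paragraph concedes that receptivity is not measured directly and proposes propensity weighting, but for the dose and fidelity analysis only.

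**The concern.** A transport refuser whom the AR2 reaches, but who accepts nothing, is in the AR2 arm under the eligibility criteria. Under the design statement that patient is in neither arm: no services were received, yet the AR2 was dispatched.

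If the design statement is followed, the AR2 arm is filtered on willingness to accept help. The comparator arm cannot be filtered in the same way, because a patient whose call came while the AR2 was busy was never offered anything. Equally unreceptive comparators therefore stay in. Matching on time and place makes the calls alike but does not make the remaining patients alike on receptivity. Willingness to accept a referral on the street and later treatment seeking are plausibly close relatives, so treatment linkage is the outcome most exposed.

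Leaving the definition open also allows the arm to be settled after outcomes are known, since the cohort is assembled retrospectively from administrative data.

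**Working it through.** **1. Who falls where (all refuse transport)**

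| Patient | Sections 2.2 and 2.3; paired section of 5.5 | 3.1 Aim 1 b | 3.1 Aim 1 d |
|---|---|---|---|
| AR2 attends, services accepted | AR2 | AR2 | not a comparator |
| AR2 attends, services declined | AR2 | neither arm | not a comparator |
| AR2 dispatched, patient leaves first | not settled | neither arm | comparator |
| AR2 busy on another call | comparator | comparator | comparator (primary) |

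Rows two and three are where the text disagrees.

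**2. The plan's own figure.** Section 5.5 gives 26% treatment seeking within 60 days, an odds ratio of 1.5 (about 35%), one-sided alpha 0.05, power 0.80 and 360 pairs. With independence within pairs, an odds ratio of 1.5 on 26% gives 34.5%.
- Discordant probabilities: 0.345 × 0.74 = 0.255 and 0.26 × 0.655 = 0.170. Their sum is 0.426 and their difference 0.0851.
- Asymptotic McNemar: N = [1.645√0.4257 + 0.8416√(0.4257 − 0.0851²)]² / 0.0851², which is just over 361, so 362 pairs.

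The plan's 360 is reproduced. At the rounded 35%, the exact McNemar test has power 0.816 with 360 pairs. The present point does not affect the sample sizes.

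**3. Effect of keeping acceptors only, with no true AR2 effect.** Let d be the share who decline and r the ratio of decliners' to acceptors' outcome rate. Neither is in the protocol; both are assumed. If the overall rate is p, then

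acceptor rate = p / [(1 − d) + d·r].

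The comparator stays at p. For linkage, p = 0.26:

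| d | r | Acceptor rate | Apparent OR | Exact one-sided false-positive rate, 360 pairs |
|---|---|---|---|---|
| any | 1 | 26.0% | 1.00 | 0.042 |
| 10% | 0.5 | 0.26/0.95 = 27.4% | 1.07 | 0.09 |
| 20% | 0.5 | 0.26/0.90 = 28.9% | 1.16 | 0.20 |
| 30% | 0.5 | 0.26/0.85 = 30.6% | 1.25 | 0.36 |
| 20% | 0.75 | 0.26/0.95 = 27.4% | 1.07 | 0.09 |
| 30% | 0.75 | 0.26/0.925 = 28.1% | 1.11 | 0.14 |

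Example: 0.306/0.694 = 0.441; 0.26/0.74 = 0.351; ratio 1.25. The asymptotic test gives slightly higher rates (0.11, 0.22 and 0.39 for d = 10%, 20% and 30% at r = 0.5).

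**4. Death and repeat overdose.** With d = 30% and decliners at 1.5 times the acceptors' risk, the divisor is 0.7 + 0.45 = 1.15.
- Death: 10%/1.15 = 8.7%, risk ratio 0.87. The false-benefit rate at 370 pairs is 0.123, against 0.039 without selection.
- Repeat overdose: 30%/1.15 = 26.1%. The rate at 105 pairs is 0.123, against 0.037.

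If decliners are instead at lower risk (r = 0.75, d = 30%), the apparent death risk ratio is 1/0.925 = 1.08 and the bias runs against the AR2.

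**The case against.** A reader might infer that the preferred paired analysis is already biased as written. The document does not support that. The paired section starts from each AR2 encounter, the time-boundary comparison also speaks of encounters, and declining services is not an exclusion. The bias enters only if the design-statement definition is carried into the analysis. This part of the objection stands.

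It can also be said that receiving services or engagement is loose wording for being attended by the AR2. SA1 contrasts it with EMS care only, and the design statement never mentions decliners. That is possible but not comfortable. Section 3.1 lists six core services, several of which need the patient's cooperation. Aim 3 records each service per dispatch, records separately whether there was any interaction, and treats engagement as something to be explained. Neither services nor engagement follows automatically from dispatch.

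The size is assumed. A full decliner must have accepted none of six services, so a share of 20% to 30% may be too high, and r may be closer to 1. This stands too, and is why a range is shown.

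Finally, defining the AR2 arm by arrival on scene is a tempting repair, but it is incomplete. Some patients leave before the AR2 arrives. They would drop out of the AR2 arm while simultaneous comparators who leave early stay in, which is again a filter on one side only.

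**Conclusion.** The inconsistency is in the text: three different markers (receipt, encounter, arrival) are used for AR2 exposure, and two (no dispatch, no arrival) for its absence. Read literally, the design statement removes decliners from one arm on a trait that the protocol says it cannot measure directly.

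The consequence is conditional. If that definition is used, it could produce a false benefit, most plausibly for treatment linkage. The apparent odds ratio would be 1.16 to 1.25, against a planned 1.5, with a false-positive rate of about 0.20 to 0.36. This assumes a 20% to 30% decline share, decliners linking at half the acceptors' rate and independence within pairs. At 0.75 times the rate it is about 0.09 to 0.14; at equal rates there is no bias. For overdose and death the direction is uncertain and could reverse. The document does not establish that a false benefit will occur. The definition should be settled before analysis.

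**What to change.** In Section 1.1 (SA1) and Section 3.1, Aim 1, b and d, state one exposure definition and use it for every Aim 1 contrast:

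- AR2 arm: the AR2 was dispatched to the call, whether or not any service was accepted. Comparator: the AR2 was not dispatched or was unavailable.
- Patients who leave before the AR2 arrives stay in the arm to which their call was assigned. An arrival-based definition can be a sensitivity analysis.
- The transport-refusal condition, now in the design statement but absent from Sections 2.2 and 2.3, is applied identically to both arms.
- Receipt of services remains the dose and fidelity variable of Aim 3.

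The cost is mainly wording. Section 4.4 already provides for AR2 dispatch and encounter data and for all EMS overdose encounters, including whether transport was refused. With no selection and no true effect, the exact one-sided rates stay at 0.037 to 0.042. The drawback is that the estimated effect may be somewhat diluted, because patients who decline or leave early are counted in the AR2 arm.

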## 1.2. Background:

The opioid crisis has hit Philadelphia particularly hard, with over 46 overdose deaths per 100,000 residents in 2017, twice the national average. In response, the City of Philadelphia developed an overarching prevention strategy, the Resilience Project, which includes both services targeted toward people who use opioids and neighborhood environment interventions that address the blighted conditions where most overdoses occur. The Resilience Project focuses on Kensington, the neighborhood with the city's highest overdose rate and high rates of poverty, homelessness, and dilapidated neighborhood conditions

Experiencing an overdose often brings people who use opioids into contact with healthcare providers and represents an opportunity to improve outcomes through harm reduction and care linkage. For example, many people are brought to Emergency Departments after overdose and are linked to care through "warm hand off" programs. However, among the 15,000 annual emergency medical services (EMS) calls in Philadelphia for overdose, up to 28% of patients refuse transport to the hospital and are, thus, at acute risk of later overdose. The Resilience Project AR2 aims to close this gap by engaging people who use opioids at the *time and place* of their overdose. The AR2 is a mobile medical unit – staffed with a social worker and paramedic – that accompanies ambulances responding to overdose calls in Kensington to engage in treatment or distribute naloxone to patients who refuse hospital transport.

Another Resilience Project program is blight remediation. The places where people live, work, and play are significant drivers of health. This is particularly important in the opioid epidemic, as blighted neighborhood conditions are associated with drug sales, substance use, and morbidity. Resilience Project blight remediation efforts include abatement of vacant lots and cleaning and sealing of abandoned houses. Changing the neighborhood context of high-risk overdose *places* such as Kensington could be an innovative method to augment opioid overdose prevention efforts, including the AR2.

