**4.4. Administration of Surveys and/or Process:**

**Process for Review of Databases:** We will use data from four different City of Philadelphia departments: Philadelphia Department of Public Health (PDPH), Philadelphia Fire Department (PFD), Department of Behavioral Health and Intellectual disAbilities, and Managing Director's Office (MDO). These data are not currently linked between departments (we have letters of support from each agency). AR2: the AR2 dispatch and encounter data will be shared from both the PDPH and PFD databases. These data include 1) date, time, and location for all AR2 interactions, 2) demographic information about each participant including name and date of birth, and home address (when available), and 3) information about which components of the AR2 intervention were delivered during each engagement and in follow up.

Data related to linkage to care outcomes will be extracted from the DBHIDS Enterprise Data Warehouse. This data system includes all Medicaid plus uninsured claims for substance abuse treatment and care in Philadelphia. There is robust Medicaid penetration among opioid users in Philadelphia. In 2017, there were over 15,000 unique beneficiaries with opioid use disorder using behavioral health services, up from 9,000 in 2010. DBHIDS has committed to sharing these data in a manner that can be linked to EMS and

AR2 visit. This ensures that we will be able to track the substantial number of people who use opioids and who remain in Philadelphia through the behavioral health system after they have come into contact with the AR2 or EMS.

Data regarding fatal opioid overdose will come from the PDPH through the Philadelphia Office of the Medical Examiner, which sits within the PDPH. These data will include the name, date of birth, and death location for all fatal opioid overdose victims. The second distal outcome is non-fatal overdose, data which will come from both the PFD and the PDPH. The PFD will provide data for all EMS overdose related encounters, including date, time, and location of the dispatch; patient name and date of birth; patient home address (when available); and outcome of encounter (refused transport vs. transport to a hospital).

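### Aim 1 compares only patients who refused hospital transport, but AR2 is dispatched before refusal is known and can change who refuses, so refusers in the two arms may differ

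*Protocol*

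**What the plan says.** Protocol section 3.1, Aim 1, part b restricts both arms by transport decision. It compares people "who overdose, refuse EMS transport, and receive AR2 services with those who refuse EMS transport but for whom the AR2 is not dispatched".

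Part c describes the order of events (the protocol uses AR2 and ARU for the same unit). The unit is sent to all presumed overdose calls in Kensington between 10 AM and 6 PM, and "The AR2 accompanies – but do not replace – conventional ambulances dispatched for these calls". Arrival order varies: "If the ARU arrives to the patient before the ambulance, the ARU team initiates medical treatment, including administration of naloxone"; "If the ARU vehicle arrives after the ambulance, ARU staff provide backup support focused on harm reduction and linkage to care as needed". On who receives the service: "The ARU delivers six core services on scene to patients who refuse transport to the hospital". These services include referral to a facility with immediate availability and transport there. By contrast, "traditional EMS does not have the capacity to refer patients to treatment programs, provide transportation directly to treatment programs, or follow up".

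Section 1.2 notes that patients who do go to hospital also have a route into treatment: "many people are brought to Emergency Departments after overdose and are linked to care through" hand-off programs.

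Section 3.1, Aim 1, part d argues that receiving EMS alone depends mostly on when and where the overdose occurs. Section 5.5, Aim 1 gives three designs: simultaneous-call pairs, a comparison across operating hours with propensity weighting if needed, and a difference-in-difference against areas outside 19134. Section 4.4 lists, among the data supplied for all EMS overdose encounters, the "outcome of encounter (refused transport vs. transport to a hospital").

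**The concern.** The design treats refusal as a characteristic the patient brings to the encounter. On the protocol's own description, dispatch comes first and the transport decision second, and one arm may have an alternative to the hospital at hand when the decision is made. Some patients who would have gone to hospital may decline because a treatment place is on offer. Others may be persuaded to go. Either way, the refusers seen with AR2 need not be the kind of patients who refuse without it.

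The argument in part d concerns who gets AR2. It does not cover who refuses once AR2 is present. A difference among refusers in linkage, repeat overdose or death could then partly reflect who was selected and not what AR2 did for them. Part c ties longer operating hours to AR2 being found effective, so the distinction matters for how the result is used.

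**Working it through.** **1. The plan's own figures.** These use a one-sided 5% test and 80% power, with outcomes assumed independent within pairs.

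| Outcome | Paired: recomputed (stated) | Across hours, per arm: recomputed (stated) |
|---|---|---|
| Death, 10% to 5% | 373 (370) | 382 (380) |
| Repeat overdose, 30% to 15% | 106 (105) | 108 (105) |
| Treatment, odds × 1.5 from 26% | 361 (360) | 383 (380) |

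The paired figures for death and repeat overdose use exact McNemar. The paired treatment figure uses the asymptotic McNemar formula; the exact test gives 383. The across-hours figures use two proportions with continuity correction. For the hazard outcome, 56 events / (0.19 + 0.095) = 197 per arm, against 200. The sample-size arithmetic is not at issue.

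**2. Whether the planned methods remove the selection.**
- *Pairing* balances time and place of the call, not the decision taken after AR2 arrives.
- *Weighting* uses age, sex, race and substance use profile. Readiness for treatment is not among them.
- *Difference-in-difference* subtracts the time-of-day difference outside 19134, where AR2 never operates. A shift in refusal caused by AR2 enters only the cell inside 19134 during AR2 hours, so it stays in the estimate.

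**3. Illustration if AR2 raises refusal and has no effect on anyone's treatment seeking.** Without AR2, refusal is taken as 28% and treatment seeking among refusers as 26%. Both are assumptions: section 1.2 gives up to 28% of overdose calls citywide, section 3.1 gives 25% to 30% for Kensington, and section 5.5 gives 26% after an overdose. None is split by AR2 presence, and the 26% is not stated to be among refusers. Refusal with AR2 (r) and treatment seeking among added refusers (q) have no source in the protocol and are varied.

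Rate among AR2 refusers = [0.28 × 0.26 + (r − 0.28) × q] / r. The odds ratio is against 0.26/0.74 = 0.351.

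| r | q = 40% | q = 50% |
|---|---|---|
| 33% | 28.1%, OR 1.11 | 29.6%, OR 1.20 |
| 38% | 29.7%, OR 1.20 | 32.3%, OR 1.36 |
| 45% | 31.3%, OR 1.30 | 35.1%, OR 1.54 |

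Example: (0.0728 + 0.05 × 0.40) / 0.33 = 0.0928 / 0.33 = 28.1%.

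**4. If AR2 lowers refusal to 20%.** The share of former refusers removed is f = 0.08/0.28 = 0.286. If they seek treatment at k times the rate of those who remain, the remaining refusers' rate is 0.26 / (1 − f + fk). For k = 0.5 this is 0.26/0.857 = 30.3%; for k = 2 it is 0.26/1.286 = 20.2%. The bias can favour AR2 or count against it.

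**5. If refusal stays at 28% but the people change.** Suppose 5 points leave (seeking treatment at 26%) and 5 points enter (at 40%). The rate is (0.0728 − 0.013 + 0.020)/0.28 = 28.5%, an odds ratio of 1.13. Equal refusal rates do not rule out selection.

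**6. Size of an analysis regardless of transport.** Assume AR2 acts only in the 28% who refuse (range 25% to 30%) and that transported patients have the same base rates. The diluted rate is p0 + 0.28 × (p1 − p0); sample sizes are one-sided with continuity correction.

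| Outcome | Diluted contrast | n per arm (range for 30% to 25%) |
|---|---|---|
| Repeat overdose | 30% to 25.8% | 1,457 (1,268 to 1,830) |
| Treatment | 26% to 28.4% | 4,391 (3,838 to 5,481) |
| Death | 10% to 8.6% | 5,463 (4,745 to 6,882) |

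The projected 600 to 1,000 engagements imply about 600/0.30 = 2,000 to 1,000/0.25 = 4,000 AR2-attended encounters, if engagements are refusers. This is an upper guide, because the primary analysis uses first encounters only and simultaneous pairs will be fewer.

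**The case against.** Part c says the six services go to patients who refuse, and the aims describe AR2 as serving people who refuse. Read literally, refusal precedes the service. AR2 may also arrive after the ambulance, and part d allows for the patient or ambulance leaving before it arrives. A reader might infer that AR2 is always present at the decision and that refusers in the two arms are in fact different. The protocol supports neither: it gives no refusal rate by AR2 presence and does not describe its services as being offered in place of the hospital. What stands is that dispatch precedes refusal, the unit can be first on scene, its support when second is not limited to people who have already refused, and no rule requires refusal to be recorded before AR2 contact.

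A second objection is that a refusal table and an extra analysis population usually belong in a SAP, which is not shown, and that the eligibility lists in sections 2.2 and 2.3 do not mention refusal. That is fair for the details. The restriction itself is fixed in the protocol's Aim 1 design, and the protocol's argument for comparability does not reach it.

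Third, the all-encounter analysis answers a different question and is weak for two outcomes. That is correct, and it limits the remedy to a sensitivity analysis.

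**Conclusion.** Aim 1 conditions both arms on a decision made after AR2 dispatch, which AR2 can influence, and none of the three designs removes the resulting selection. Refusers may differ systematically between arms; the direction is unknown. With no AR2 effect, and with the assumed inputs above, a rise in refusal to 33% to 45% gives an apparent linkage odds ratio of about 1.1 to 1.5, against a planned 1.5. If refusal falls, the sign depends on who is persuaded.

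Two stronger readings should be resisted. The planned effect as a whole could be an artefact only in the most extreme combination, where refusal rises from 28% to 45% and half of the added refusers seek treatment. Nor do the documents show that any linkage gain would be pure substitution for hospital hand-off: patients diverted from hospital might have been linked there, but the protocol gives no figure for how many.

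The bias is zero if AR2 does not change who refuses, or if those who switch have the same risk as those who refuse either way.

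**What to change.** Keep the refuser analysis, and add to section 3.1, Aim 1, part b and to section 5.5, Aim 1:

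1. A comparison of the proportion refusing transport, and of refusers' measured characteristics, between AR2-attended and comparator encounters, in the same pairs and hour bands.
2. The same outcome analyses in all eligible overdose encounters regardless of transport, using the transport field in section 4.4, reported with confidence intervals beside the refuser result.
3. A statement that the refuser result is conditional on refusal and open to selection through changed transport decisions.

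Do not use similar refusal rates, or an all-encounter estimate in the same direction, as a rule for clearing the refuser result. Equal rates can hide switching both ways (step 5), and with no true effect an estimate takes the favourable sign about half the time.

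The cost is one table, some wording and one further run on data already requested. The drawback is dilution, since only about 25% to 30% refuse. The all-encounter analysis is likely adequate for repeat overdose, but underpowered for death and, over most of the projected range, for treatment linkage. It should be labelled a sensitivity analysis.
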